The community survey sample size was determined to estimate differences in mean reduction in systolic blood pressure among those with diagnosed hypertension in the community. First, we computed the base sample size required to detect a desired effect size of 5 mmHg given the SBP standard deviation of 18.5, power = .80 and α = .05, based on the mPower Heart Study [24]. We estimated that 168 individuals with hypertension would be needed to detect the anticipated effect size. Second, we estimated that we would require a sample size of 839 adults in the general population to identify 168 individuals with hypertension, assuming prevalence of diagnosed hypertension of 20%. Third, we determined the optimal sample allocation for a multi-stage sampling design that would be time-efficient for field work and statistical precision. We assumed an intraclass correlation of systolic blood pressure of 0.018 based on village-level clustering of SBP in the DISHA study [32] (unpublished findings). After applying a 10% refusal rate based on our prior field studies in the region, we determined that a cluster size of 50 adults per village distributed across 35 villages per block was optimal. This yielded a total sample size of 3508 for the community survey to be evenly split between the program and comparison blocks.

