#### Health outcomes among patients receiving the I-TREC program

Using patient health data from the eCRF, we will assess processes of care and changes in blood pressure and blood glucose outcomes over time among patients with hypertension or diabetes who seek care at I-TREC program facilities in a facility-based evaluation component. Because I-TREC is being integrated into the routine care in the program block under real-world conditions, we will not be assigning individual patients to treatment nor actively following patients for research visits. Rather, all adults residing in the I-TREC catchment area (i.e., residents of Mukandpur block) will be exposed to the program and patient data will be collected every time a person chooses to receive care at a government health facility. Data from all patients visiting facilities in the program block captured in the Government of India eCRF will be de-identified and obtained by AIIMS throughout the program period for monitoring and evaluation purposes.

The sample size for the facility-based evaluation is out of our control and contingent on the number of patients who seek care at government facilities. We therefore report the detectable effect size for longitudinal change in systolic blood pressure over time in patients at I-TREC facilities after setting power to 80% and α = .05. The program block, Mukandpur, has a population of 98,000. We expect that 30% of the local population will seek care at a government facility, 50% will be age-eligible (30 years and older) per the government guidelines for universal and opportunistic screening of hypertension and diabetes, and 20% will test positive for hypertension, amounting to an estimated patient pool of 2940 adults. Assuming that 50% of all enrolled patients with hypertension and diabetes make repeat visits (enabling us examine changes in outcomes), we will be able to detect a 1.35 mmHg difference in SBP.

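### The base of 168 hypertensives per block matches an unannounced one-sided .05 test; a two-sided .05 test needs 215 in the same two-group formula

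*Protocol article*

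**What the plan says.** The sample-size paragraph of the community survey section sets the target: "we computed the base sample size required to detect a desired effect size of 5 mmHg". The remaining inputs to that step read: "given the SBP standard deviation of 18.5, power = .80 and α = .05". Its result is "We estimated that 168 individuals with hypertension would be needed to detect the anticipated effect size". The next step requires "a sample size of 839 adults in the general population to identify 168 individuals with hypertension, assuming prevalence of diagnosed hypertension of 20" (per cent). The paragraph then gives the clustering and refusal inputs, "We assumed an intraclass correlation of systolic blood pressure of 0.018" and "After applying a 10% refusal rate based on our prior field studies in the region", and concludes that "a cluster size of 50 adults per village distributed across 35 villages per block was optimal". The total is 3508, split evenly between the blocks.

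The following section, on health outcomes among patients receiving the program, uses the same power and the same alpha value. From a pool of 2940 patients, half of whom make repeat visits, it states that "we will be able to detect a 1.35 mmHg difference in SBP". It gives no SD. Neither section says whether alpha is one-sided or two-sided.

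The statistical analysis section makes the group-by-period interaction from a GEE model the effect estimate and mentions no one-sided test.

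**The concern.** An alpha of .05 with no qualifier is normally read as two-sided. On that reading the printed inputs do not give 168. The figure matters because 839 and 3508 are both built on it. A reader who later weighs a null endline result, reported with an ordinary 95% confidence interval, will assume that the survey had 80% power for 5 mmHg by the article's own derivation. The facility calculation carries the same alpha label but appears to use it differently, so the article does not settle what was meant.

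**Working it through.** **Inputs.** Difference 5 mmHg, SD 18.5, power .80, alpha .05, prevalence 20%, ICC 0.018, 10% refusal, 50 adults per village and 35 villages per block, all from the community survey section. The pool of 2940 and the 50% repeat-visit share come from the facility section.

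**1. Is 168 per block or in total?**
- 839 × 0.20 = 167.8.
- Design effect: 1 + 49 × 0.018 = 1.882.
- 839 × 1.882 / 0.9 = 1754.4; doubled, 3508.9, against 3508 stated.

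The chain reaches 3508 only if 168 is per block. Read as a two-block total (84 each), it would give only 41.7% power two-sided or 54.2% one-sided.

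**2. Which formula gives 168?** For two means, n per group = 2 (z_alpha + z_power)² SD² / difference².
- Two-sided: 2 × (1.960 + 0.8416)² × 18.5² / 25 = 214.9, so 215.
- One-sided: 2 × (1.645 + 0.8416)² × 18.5² / 25 = 169.3, or 168.4 with z rounded to 1.64 and 0.84.
- One-sample or paired: 107.5 two-sided, 84.6 one-sided.
- Difference-in-difference of four independent cells: about 430 per cell two-sided, 339 one-sided.

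Only the one-sided two-group version is near 168.

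**3. What 168 effective per block gives.** 5 / (18.5 × √(2/168)) = 2.477. Power is 69.7% two-sided and 79.7% one-sided. The two-sided detectable difference at 80% power is (1.960 + 0.8416) × 18.5 × √(2/168) = 5.66 mmHg.

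**4. Facility figure, assuming SD 18.5 carries over.** n = 2940 × 0.5 = 1470.
- Two-sided: 2.8016 × 18.5 / √1470 = 1.352.
- One-sided: 2.4865 × 18.5 / √1470 = 1.200.

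The stated 1.35 matches the two-sided value.

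**5. What 3508 gives with the design effect for the analysed subgroup.** The comparison is among diagnosed hypertensives, not all 50 adults per village.
- Per block: 1754 × 0.9 × 0.20 = 315.7, or 315.7 / 35 = 9.02 per village.
- Design effect: 1 + 8.02 × 0.018 = 1.144.
- Effective number: 315.7 / 1.144 = 276 per block.
- Simple two-group comparison: 5 / (18.5 × √(2/276)) = 3.175, two-sided power about 89%.

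**6. The planned difference-in-difference.** This assumes 3508 in each survey round and four independent cells of 276 effective hypertensives.
- 5 / (18.5 × √(4/276)) = 2.245, two-sided power about 61%.
- Detectable difference at 80% power: 2.8016 × 18.5 × √(4/276) = 6.24, about 6.2 mmHg.

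**The case against.** The strongest reply is that the article states no sidedness, so 168 contradicts nothing printed: one-sided .05 reproduces it to within two people, and a condensed article may leave sidedness to the full protocol. It stands that one-sidedness is inferred by back-calculation. But the article prints both inputs and result, they disagree under the usual meaning of alpha, and no section announces the other meaning.

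A second reply concerns the facility figure. That section gives no SD, and 18.5 need not apply to within-patient change. A one-sided test with a change SD of about 20.8 would also give 1.35 (2.4865 × 20.8 / √1470 = 1.35). This stands. A reader might infer a proven contradiction between the two calculations; the documents support only an apparent one, conditional on SD 18.5.

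A third reply is that the survey is not short for a two-group comparison, because the design effect for 50 adults is applied to about 9 hypertensives per village. This also stands: 276 effective exceeds 215. A reader might infer that 3508 should be scaled up by 215/168, or that the survey really has only 70% power. Neither follows, because both inherit the 1.882. The allowance still does not make 168 the right base; it offsets the shortfall without being declared.

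Finally, a reader might infer that a one-sided base leaves a harmful change untestable. A sizing convention does not restrict the analysis, and the analysis section specifies no one-sided test.

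**Conclusion.** The point holds for the base figure. With 5 mmHg, SD 18.5, power .80 and two-sided .05, the two-group base is 215 per block, so the stated 168 is 47 people (22%) lower. It corresponds to a one-sided .05 test that the article never declares. The per-block reading follows from the chain to 3508, not from an explicit statement.

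The consequence for the survey depends on the design effect. With the plan's 1.882, two-sided two-group power is about 70%; with about 1.14 it is about 89%. Neither describes the planned analysis. For the difference-in-difference, power is about 61% for 5 mmHg on the assumptions in step 6, which also take prevalence, refusal and ICC as the article states them. Correcting 168 to 215 alone would therefore replace one incomplete figure with another.

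**What to change.** In both the community survey and facility sections, state that alpha = .05 is two-sided, and give the SD used for the 1.35 mmHg figure. In the community survey section, say that 168 corresponds to one-sided .05 and that the two-sided two-group base is 215 per block. Keep 3508. Then restate the two-sided power or detectable difference it gives for the planned difference-in-difference, showing the design effect and whether 3508 is per survey round. On the assumptions above, that is about 61% power for 5 mmHg, or 80% power for about 6.2 mmHg.

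The cost is a short correction of two paragraphs. Baseline collection is already complete, and no participants are added. The stated power for the planned analysis becomes less favourable than 80%.

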#### Health outcomes among patients receiving the I-TREC program

Using patient health data from the eCRF, we will assess processes of care and changes in blood pressure and blood glucose outcomes over time among patients with hypertension or diabetes who seek care at I-TREC program facilities in a facility-based evaluation component. Because I-TREC is being integrated into the routine care in the program block under real-world conditions, we will not be assigning individual patients to treatment nor actively following patients for research visits. Rather, all adults residing in the I-TREC catchment area (i.e., residents of Mukandpur block) will be exposed to the program and patient data will be collected every time a person chooses to receive care at a government health facility. Data from all patients visiting facilities in the program block captured in the Government of India eCRF will be de-identified and obtained by AIIMS throughout the program period for monitoring and evaluation purposes.

The sample size for the facility-based evaluation is out of our control and contingent on the number of patients who seek care at government facilities. We therefore report the detectable effect size for longitudinal change in systolic blood pressure over time in patients at I-TREC facilities after setting power to 80% and α = .05. The program block, Mukandpur, has a population of 98,000. We expect that 30% of the local population will seek care at a government facility, 50% will be age-eligible (30 years and older) per the government guidelines for universal and opportunistic screening of hypertension and diabetes, and 20% will test positive for hypertension, amounting to an estimated patient pool of 2940 adults. Assuming that 50% of all enrolled patients with hypertension and diabetes make repeat visits (enabling us examine changes in outcomes), we will be able to detect a 1.35 mmHg difference in SBP.

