#### Health facility and patient assessments

Pre- and post-program health facility and patient assessments include 1) a health facility form; 2) patient flow mapping; and 3) patient out-of-pocket cost of care surveys. Health facility forms will be completed at all 52 government health facilities (21 in program and 30 in control and the common District Hospital) to describe the infrastructure, facility personnel and salaries, availability of medications, and availability of diagnostics and laboratory investigations. Health facility form completion requires a combination of observational checklists and structured interviews with administrators. Patient flow mapping entails identifying and following patients with hypertension and diabetes through typical visits to map the typical workflow, diagnostic and prescription practices, and duration of visits. Together, the health facility form and patient flow mapping will provide data to describe the resources (time and costs) associated with typical healthcare visits for patients with hypertension and diabetes with and without the I-TREC program. Patient cost surveys will be used to obtain data on expenditures related to outpatient and inpatient health care utilization in the last 3 months to understand the cost incurred by patients to manage their disease. Administration of the pre- and post-program patient cost surveys will contribute data to understand whether the program has any impact on patient expenditures related to hypertension and diabetes. Purposive sampling will be done to recruit patients for the patient flow mapping and cost surveys.

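### The facility component's detectable difference of 1.35 mmHg treats 1470 patients as independent and uses an SD of SBP for a within-patient change; it should be restated as a range

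*Protocol article*

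**What the plan says.** The section on health outcomes among patients receiving the I-TREC program reports a "detectable effect size for longitudinal change in systolic blood pressure over time in patients at I-TREC facilities after setting power to 80" per cent, with α = .05. The number of patients is built up in steps:

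- Mukandpur, where the program runs, is taken to have 98,000 inhabitants.
- "We expect that 30% of the local population will seek care at a government facility, 50% will be age-eligible".
- "20% will test positive for hypertension, amounting to an estimated patient pool of 2940 adults".
- Half of the enrolled patients are assumed to make repeat visits, so that a change can be measured.

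The conclusion is that "we will be able to detect a 1.35 mmHg difference in SBP". The section states no SD, ICC, design effect or number of facilities for this calculation.

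Three other places bear on it:

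- The community survey section gives an SBP standard deviation of 18.5 and says "We assumed an intraclass correlation of systolic blood pressure of 0.018 based on village-level clustering of SBP".
- The section on health facility and patient assessments counts the sites as "21 in program and 30 in control and the common District Hospital".
- Table 1 places the combined eCRF and CDSS at Primary Health Centres, Community Health Centres and the District Hospital. At Sub-Centres it lists the eCRF alone, for screening and referral.

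**The concern.** Patients at one facility share clinicians, drug stock, diagnostics and CDSS advice tailored to that level of care. If response to treatment differs between facilities, their SBP changes are correlated, and 1470 patients carry less information than 1470 independent ones. The article allows for this with villages in the survey, then prints a finished power statement for the facilities without it. The SD in the formula also appears to be that of a single SBP reading, while the quantity analysed is a change.

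This is the only precision statement for the facility component. Reduction in mean blood pressure at program facilities is a key effectiveness indicator in Table 2, and the Summary says no comparable patient data exist in the comparison block. A reader will take 1.35 mmHg as the precision on offer. If the analysis made the same independence assumption, its confidence intervals would be too narrow by about the square root of the design effect.

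**Working it through.** **Inputs.** Population 98,000, shares 30%, 50% and 20%, repeat visits 50%, power 80%, α .05 (facility outcomes section). SD 18.5 and ICC 0.018 (community survey section). 21 program facilities plus one shared District Hospital (facility assessments section). Sidedness is not stated; two-sided reproduces the figure.

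**1. Reproduce the printed figure.**

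- Pool: 98,000 × 0.30 × 0.50 × 0.20 = 2940. With repeat visits: n = 2940 × 0.50 = 1470.
- One-sample formula: (1.960 + 0.842) × 18.5 / √1470 = 51.83 / 38.34 = 1.352 mmHg. This matches 1.35.
- Variants: one-sided gives 1.20; two groups of 1470 give 1.91; two groups of 735 give 2.70; one sample of 2940 gives 0.96. Two groups of 2940 also give 1.352, because the algebra is identical, but that ignores the repeat-visit step. Neither matching form contains a design effect.

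**2. Compare with the survey calculation.**

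- Design effect: 1 + (50 − 1) × 0.018 = 1.882.
- 839 × 1.882 = 1579; divided by 0.9 for refusals, 1754 per block; two blocks give about 3508, the printed total.

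So the survey figure includes clustering of SBP and the facility figure does not.

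**3. Add clustering by facility.** With k equal facilities, m = 1470/k and DE = 1 + (m − 1) × ICC. The detectable difference is 1.352 × √DE. Power at 1.35 mmHg is Φ(1.35 / (18.5 × √(DE/1470)) − 1.96). For k = 21, m = 70. The ICC of SBP change by facility is not in the documents, so every value below is an assumption; 0.018 is borrowed from the survey.

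| ICC | DE | Detectable difference (mmHg) | Power at 1.35 mmHg |
|---|---|---|---|
| 0 (as printed) | 1.00 | 1.35 | 80% |
| 0.001 | 1.07 | 1.40 | 77% |
| 0.005 | 1.35 | 1.57 | 67% |
| 0.01 | 1.69 | 1.76 | 58% |
| 0.018 | 2.24 | 2.02 | 46% |
| 0.05 | 4.45 | 2.85 | 26% |

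Counting the District Hospital (k = 22), ICC 0.018 gives 2.00 mmHg and 47%. With 10 treating sites (an assumption), it gives DE 3.63, 2.57 mmHg and 31%. A t reference on 20 degrees of freedom lowers the 46% for 21 facilities to 43%.

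**4. Use the SD of a change.** If both readings have SD 18.5 and visit-to-visit correlation r, the SD of change is 18.5 × √(2(1 − r)). It equals 18.5 only at r = 0.5. The correlation is not given, so r is an assumption.

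| r | SD of change | No clustering | ICC 0.005, 21 sites | ICC 0.018, 21 sites |
|---|---|---|---|---|
| 0.3 | 21.9 | 1.60 mmHg | 1.86 mmHg | 2.40 mmHg |
| 0.5 | 18.5 | 1.35 mmHg | 1.57 mmHg | 2.02 mmHg |
| 0.7 | 14.3 | 1.05 mmHg | 1.21 mmHg | 1.57 mmHg |

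The two corrections can pull in opposite directions. At r = 0.7 and ICC 0.005 the result, 1.21 mmHg, is better than the printed figure.

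**The case against.** A reader might infer that, under the protocol's own ICC, true power at 1.35 mmHg is 46% or less. The documents do not support that. The 0.018 describes SBP level, by village, in a community sample; the facility analysis concerns within-patient change, by facility. A constant facility level cancels out of a change score, so the relevant ICC may be smaller. It may also be larger, because differences in treatment response do not cancel, and the article itself expects availability of drugs, diagnostics and clinicians to affect effectiveness. Nor are 21 facilities the most favourable count, since the District Hospital makes 22.

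It is equally tempting to say that 1.35 mmHg must overstate precision. That is not established either, because a visit-to-visit correlation above 0.5 could cancel the loss.

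Four further objections deserve weight:

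- **All program facilities are included, and patients move between them.** Treating facilities as random is an inferential choice, and equal nested clusters are a simplification. But the stated aim is a scalable model, and for that inference variation between facilities matters.
- **The analysis may handle clustering anyway.** The article says only that change in patient outcomes will be evaluated, and the variance estimator may properly sit in a document not shown. Its absence is not the point here; the printed power figure is.
- **Nothing was sized on 1.35 mmHg.** The section says the sample is outside the investigators' control. At 5 mmHg, the survey's target effect, power stays at 99% (94% with a t reference on 5 degrees of freedom) even with 6 sites, ICC 0.018 and SD 18.5. This limits the consequence but does not make the figure right.
- **The printed arithmetic is correct.** That is so. The fault lies in what it assumes.

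**Conclusion.** The point stands as a defect in a stated precision figure. The 1.35 mmHg rests on independent patients and on an SD of SBP level used for a change, and the article treats clustering of SBP differently one section earlier. That 18.5 was the SD used is inferred from the exact reproduction, since the facility section states none.

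The size cannot be fixed from the documents. At SD 18.5 with 21 equal facilities, the detectable difference is 1.40 to 2.85 mmHg over ICCs of 0.001 to 0.05, and about 2.0 mmHg if the survey's 0.018 is borrowed. Treating sites are probably fewer than 21, because the combined eCRF and CDSS starts at Primary Health Centre level, and fewer sites raise the figure. A correlation above 0.5 lowers it. No sample size or design decision depends on the number, but the claim should be corrected before it is used to interpret the facility results.

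**What to change.** In the section on health outcomes among patients receiving the I-TREC program, replace the single 1.35 mmHg with a detectable difference that includes 1 + (m − 1) × ICC by facility and uses the SD of change. Show it as a range over ICC, number of treating sites and visit-to-visit correlation. State the SD and the number of Primary Health Centre, Community Health Centre and District Hospital sites assumed. One reference point would be about 2.0 mmHg at ICC 0.018, 21 to 22 sites and SD 18.5, with that ICC labelled as borrowed from the survey.

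To match, estimate facility SBP change with variance clustered by facility and a small-sample correction, since there are few facilities.

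The cost is a probably less favourable stated figure and wider confidence intervals for the facility results. No further patients or data collection are required.

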#### Process measures

In the program block, we will examine measures of adoption and implementation of the IT tools, such as completeness of eCRF forms, acceptance (partial and full) and rejection of the CDSS advisories, time stamp of data entry, the initials of the enterer, and average number of new records per day. In both the program and comparison block, data regarding the total number of patients recorded in the out-patient registry at the facility, numbers screened for hypertension and diabetes, numbers receiving medication from the pharmacy, and numbers referred to higher level facilities will be collected through a combination of paper-based registries and routine NPCDCS reports. The I-TREC evaluation team will obtain these facility-level data using abstraction forms without removing any paper records from premises. In addition, the I-TREC evaluation team will periodically conduct random, unannounced visits to directly observe the number of patients seeking care for hypertension and diabetes facilities in both blocks. Additional data on intervention fidelity measures (e.g., use of eCRF during health visit, measurement of blood pressure and blood glucose, provision of the I-TREC print out to the patient) will also be collected through patient exit interviews and the eCRF backend data.

